### Statistical analysis

All statistical analyses will be performed using the SPSS 22.0 statistical software. Descriptive statistics will be used for baseline characteristics data. Quantitative variables (numerical variables) will be analyzed by the normality test (such as *Shapiro-Wilk*), and normal distribution numerical variables will be compared using two independent *t*-tests or analysis of variance (*ANOVA*) and other potential confounding variables (such as multicenter characteristics) as covariates. Numerical variables will be summarized with mean ± SD. Non-parametric tests (*Wilcoxon rank-sum* test, *Kruskal–Wallis* test) and M (P_25_, P_75_) will be used to describe the non-normal distribution. Qualitative variables (categorical variables) are represented by the number of cases and the composition ratio; comparison among groups will be performed using the chi-square test or Fish precision probability. Non-parametric test or analysis of covariance will be used to compare the difference in therapeutic indexes. The efficacy analysis adopts the intention to treat (ITT) analysis and the per-protocol set (PPS). Subgroup analysis will be performed regardless of whether the treatment significant effect the main outcome. Safety analysis will be performed by analyzing the incidence of intergroup AEs and abnormal laboratory examination results before and after treatment.

The full analysis set (FAS) will be conducted for the therapeutic indexes of all subjects included in the study. Statistical analysis in accordance with PPS will be conducted for the therapeutic indexes of subjects completing the drug intervention for 6 months. FAS uses the last-observed-carried-forward method (LOCF) to adjust the missing data and complete ITT analysis. The safety analysis will be performed using the safety analysis set (SS). All statistical tests will be two-sided. *p* ≤ 0.1 means there is a statistical difference, *p* ≤ 0.05 represents a significant statistical difference.

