#### Diagnostic criteria of cerebral small vascular disease

According to the “Chinese Consensus on Diagnosis and Therapy of CSVD” (Huang, 2015) and Standards for ReportIng Vascular changes on nEuroimaging (STRIVE v1) (Wardlaw et al., 2013), CSVD is primarily characterized by stroke (small deep infarction and cerebral hemorrhage), cognitive and emotional impairment and overall functional decline. Based on brain MRI, prominent manifestations include lacunar infarction (LI), WMH, dVRS, CMB, and cerebral atrophy (Figure 3). The imaging features include:(1) Number of LI: (a) Old LI: round or oval, with a maximum diameter not exceeding 15mm, distributed under the cortex, T1 and T2 are cerebrospinal fluid signals and T2 fluid-attenuated inversion recovery (FLAIR) is a ring of low signal in the center and high signal around it; (b) Acute LI: round or oval, with a maximum diameter not exceeding 15 mm, subcortical distribution, high signal on diffusion-weighted imaging (DWI) and negative on conventional MRI.(2) WMH of vascular origin: It shows abnormal signals, and different ranges and sizes in the white matter. Such as an equal signal or low signal in T1, a high signal in T2, or T2 FLAIR without a cavity. The severity of cerebral white matter lesion (WML) is based on the Fazekas scores (Fazekas et al., 1987); for instance, changes in paraventricular hyperintensity, such as no lesions, cap-like or pencil-thin lesions, smooth halo, irregular paraventricular hyperintensity, extend to the deep white matter, rated as 0, 1, 2, and 3 points respectively; the signal changes in the deep white matter, such as no lesions, spot-like or small-piece lesions, extensive patchy lesions beginning to fuse and large-area fusion of lesions, score 0, 1, 2 and 3 respectively. The total scores are 0–6 points. WMH caused by other non vascular diseases should be excluded, such as multiple sclerosis, white matter dystrophy, etc.(3) dVRS grades (Doubal et al., 2010): The gap that passes through the gray or white matter and is consistent with the course of blood vessels. Round or oval or linear, with smooth margins, maximum diameter exceeds 3 mm, located in the distribution area of perforating arteries, all sequences are consistent with cerebrospinal fluid signal, T2 FLAIR has no surrounding hyperintensity ring (except when it crosses the WMH area), DWI has no diffusion restriction. (a) In the basal ganglia, the level with the most dVRSs prevails, and the severity is rated as 4. The classification is as follows: Grade 0 = no dVRS, Grade 1 ≤ 5 dVRS, Grade 2 = 5–10 dVRS, Grade 3 ≥ 10 dVRS, but the number of dVRS is still countable. The number of dVRS Grade 4 is difficult to count, and Grade 4 has cribriform changes in the basal ganglia. (b) In the white matter area, dVRS severity scoring criteria: Grade 0 = no dVRS, Grade 1 ≤ 10 dVRS, Grade 2 ≥ 10 dVRS (but the largest level of dVRS is < 10), Grade 3 = 10–20 dVRS at the maximum number level and Grade 4 ≥ 20 dVRS at the maximum number level.(4) CMB: Round or oval, well-defined, homogeneous susceptibility-weighted imaging (SWI) signal focal [computed tomography (CT) is not shown in T1, T2, T2 FLAIR], the diameter is 2–10 mm, and the lesion is surrounded by brain parenchyma. A hypointense signal <2 mm seen on 1.5T MR may only be the missing signal in one voxel, and the artifact cannot be ruled out.(5) Cerebral atrophy: Reduction of brain volume unrelated to specific focal injury.

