### Data collection

#### Baseline data

Baseline data, including general demographic information, past medical history, symptoms and signs, history and treatment of HT, brain MRI, TCM syndrome scores, cognitive and depression scales and safety evaluations will be collected. The content includes the subject’s Age, gender, occupation, body mass index (BMI) and clinical BP, main symptoms and signs, history of basic diseases and medication, TCM syndrome scores, mini-mental state examination (MMSE) and Hamilton depression (HAMD)-17 scores, brain MRI (Fazekas scores, dVRS grades, number of LI and CMB), electrocardiograph (ECG) and laboratory parameters including blood routine, urine and stool routine, liver and kidney function, blood lipids, fasting plasma glucose (FPG), glycosylated hemoglobin A1c (HbA1c), myocardial enzyme spectrum and coagulation routine.

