### Types of outcomes

#### Primary outcome

The Fazekas scores and dVRS grades will be obtained for both groups. The specific scoring criteria are described in the diagnostic criteria. Brain MRI examinations will be performed before enrollment and after 6 months of treatment.

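### The normality gate tells nothing about an integer Fazekas score, and the plan leaves rank test or ANCOVA open without naming baseline score or stratum as covariates

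*Protocol article*

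**What the plan says.** The protocol article, Statistical analysis, opens with a gate: "Quantitative variables (numerical variables) will be analyzed by the normality test", with Shapiro-Wilk as the example and no threshold given. Variables that pass go to a t-test or ANOVA, "and other potential confounding variables (such as multicenter characteristics) as covariates". For those that do not pass, the Wilcoxon rank-sum or Kruskal-Wallis test with median and quartiles "will be used to describe the non-normal distribution"; no covariate is mentioned on this branch.

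A later sentence of the same section addresses efficacy directly: "Non-parametric test or analysis of covariance will be used to compare the difference in therapeutic indexes". It states no rule for choosing between the two methods and lists no covariates.

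The outcomes concerned are discrete. Under Primary outcome, "The Fazekas scores and dVRS grades will be obtained for both groups". Under Diagnostic criteria of cerebral small vascular disease, Fazekas is the sum of two 0–3 sub-scores ("The total scores are 0–6 points"), and dVRS is graded 0 to 4.

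Baseline values exist for everyone. The Baseline data section lists "brain MRI (Fazekas scores, dVRS grades, number of LI and CMB", and Primary outcome adds that "Brain MRI examinations will be performed before enrollment and after 6 months of treatment". The Y/N symptom stratum is fixed at randomisation.

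**The concern.** A normality pre-test can only inform the choice of method if it may go either way. A score with seven possible integer values will not look normal to Shapiro-Wilk once a group has several dozen patients. The pre-test then acts as a fixed switch to the branch without covariates.

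Three things are at stake. First, the rank branch reports medians and quartiles, whereas the trial is sized on a 0.5-point difference in means. Second, the month-0 Fazekas score is likely to predict the month-6 score, and not adjusting for it can cost precision and leaves chance baseline imbalance in the comparison. Third, the efficacy sentence offers two methods without a rule, so a reader cannot tell which result is the primary one.

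**Working it through.** **Inputs.** From Sample size calculation: means and SDs 2.29 (1.26) and 2.8 (1.3), difference 0.5, alpha 0.10 two-sided, power 0.80, dropout 20%, total 388. From Randomization: 194 numbers per stratum, 1:1, hence 194/2 = 97 per cell (one arm within one stratum). Completers: 97 × 0.8 = 77.6, taken as 77. The correlation between baseline and month-6 score (rho) is not in the document; 0.3, 0.5 and 0.7 are assumed.

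**1. The plan's own figure.** Pooled variance = (1.26² + 1.3²)/2 = 1.6388, SD = 1.280. With the plan's rounded z values, (1.65 + 0.85)² × 2 × 1.6388 / 0.5² = 81.94, printed as 81. Unrounded z values give 82 after rounding up. The figure reproduces to within one patient, and the formula is an unadjusted comparison of two means.

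**2. Does the gate discriminate?** Normal scores with the plan's means and SDs were rounded to integers and clipped to 0–6, with 2,000 samples for each group size. Share rejected by Shapiro-Wilk, over the two arms' distributions:

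| n per group | at 0.05 | at 0.01 |
|---|---|---|
| 40 | 84–99% | 38–53% |
| 60 | 100% | 86–99% |
| 77, 81, 97, 155, 194 | 100% | 100% |

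Integer change scores (assumed probabilities 0.10, 0.45, 0.35, 0.10 for −1, 0, 1, 2) were also rejected at 0.05 in 100% of 1,000 samples at each of 81, 97, 155 and 194 per group. dVRS grades were not simulated; they have even fewer distinct values.

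**3. What baseline adjustment is worth.** ANCOVA multiplies the residual SD by √(1 − rho²). Unadjusted SE at 77 per cell = 1.280 × √(2/77) = 0.206. Power = Φ(0.5 / [0.206 × √(1 − rho²)] − 1.645).

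| rho | √(1 − rho²) | power at 77 per cell | n per group for 80% |
|---|---|---|---|
| none (unadjusted) | 1 | 78% | 82 |
| 0.3 | 0.954 | 82% | 74 |
| 0.5 | 0.866 | 88% | 61 |
| 0.7 | 0.714 | 96% | 42 |

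**4. Simulation on the integer scale** (77 per cell, alpha 0.10, 1,500 runs for each rho):

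| rho | Wilcoxon, month-6 score | Wilcoxon, change | ANCOVA |
|---|---|---|---|
| 0.3 | 0.76 | 0.64 | 0.80 |
| 0.5 | 0.73 | 0.74 | 0.85 |
| 0.7 | 0.76 | 0.90 | 0.94 |

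The rank test on the month-6 score gains nothing from a higher correlation. The rank test on change does use the baseline, but it stays below ANCOVA at each of these correlations and is the weakest of the three at 0.3.

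**5. Pooled strata.** With both strata combined, 194 × 0.8 = 155 completers per arm, unadjusted power for 0.5 points is already 96%, rising to between 97% and over 99% with adjustment. There the gain is mainly a narrower interval, not power.

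**The case against.** A reader might infer that the plan prescribes an unadjusted rank test for the primary outcome and throws the baseline score away. The text does not say so. The normality sentences follow the one on baseline characteristics and concern numerical variables in general. The one sentence about the therapeutic indexes expressly allows ANCOVA. The word difference in it may mean change from baseline, and a rank test on change would use the baseline. Nor does the section say whether Fazekas and dVRS count as quantitative or categorical. All of this stands, and it limits the point to a gate that does not work and a choice left open.

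A reader might also infer that the pre-test distorts the type I error. A gate that always rejects is deterministic, so it amounts to a plain Wilcoxon test, whose error rate is sound. Only the unruled choice between a rank test and ANCOVA could let the data steer the method, and no size can be put on that.

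A third inference, that the sample size is wrong on this account, fails as well: it was computed without adjustment and does not depend on it.

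Finally, one may say that model terms belong in a fuller document and that a Wilcoxon test on an ordinal score is valid in a randomised trial that calls itself exploratory. The validity is granted. But the gate is a rule that the article states, not a detail it leaves out, and it is a poor rule for these outcomes.

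**Conclusion.** The point holds in this limited form. If Fazekas is treated as a quantitative variable, the stated gate leads essentially always to a rank test without covariates. The separate efficacy sentence permits ANCOVA but does not settle when. Neither route names the baseline MRI score or the Y/N stratum, although both are available for every participant. The result would be valid but may not be expressed as the mean difference the trial was sized on.

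The loss of precision depends on a correlation that the document does not give. Within a stratum, at the plan's own alpha, power for 0.5 points moves from about 78% to 82% at 0.3, to 88% at 0.5 and to 96% at 0.7: a small gain at the low end and a large one at the high end. These figures assume the plan's means and SDs, 20% dropout and comparison within stratum. This is an improvement that should be made, not an error that invalidates the trial.

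**What to change.** Remove the normality gate for efficacy outcomes and fix one primary analysis for each primary outcome before the randomisation codes are opened:

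- **Fazekas:** ANCOVA of the month-6 score on treatment, baseline score, Y/N stratum and centre, with robust standard errors, reported as an adjusted mean difference with its confidence interval.
- **dVRS grades:** a proportional-odds model with the same terms, using the baseline dVRS grade.
- **Sensitivity analysis:** the Wilcoxon rank-sum test, stating whether it is applied to the month-6 score or to the change.

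Replace the efficacy sentence that offers two alternatives with this specification. The cost is wording only: the MRI scores, stratum and centre are already collected, and standard software fits both models. If the codes have already been opened, the baseline-adjusted analysis can still be reported, but labelled as specified after unblinding.

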## Methods and analysis

### Study design

This study is a multicenter, randomized, double-blind, placebo-controlled clinical trial that will last for 13 months, including 4 weeks of the run-in period, 6 months of treatment period, and the 12th month follow-up period. Participants will be first recruited for a baseline screening, evaluation and washing-out the drug whose efficacy is similar to that of the investigational products (IP) (such as the Chinese medicine for nourishing Qi and activating blood circulation) in the run-in period. Eligible participants will be randomly classified into the intervention group and control group (all participants will be visited once after the 3rd and 6th month of treatment, respectively). Participants will be assessed with a relevant scale or laboratory biochemical examination on the scheduled day for each treatment and follow-up period. The flowchart and schedule of the trial, including a schedule of enrollment, interventions, and assessments are shown in Figures 1, 2. The trial protocol is written as per the SPIRIT-TCM Extension 2018 Statement checklist. The structured study summary is described in Table 1 according to the World Health Organization Trial Registration Dataset.

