### Group assignment and intervention

Participants will be stratified and denoted by Y or N according to the presence or absence of clinical manifestations of brain damage (cognitive decline, mood disorders, swallowing disorders, unstable gait, prolonged dizziness). Y and N groups will be divided into intervention groups (denoted by Y-T and N-T) and control groups (denoted by Y-C and N-C) using the stratified block randomized method with SAS statistical software.

Different doses of NTF capsules will be given to the Y-T and N-T groups, i.e., the Y-T group will be administered 4 capsules thrice daily with warm water, half an hour after breakfast, lunch, and dinner. In contrast, the N-T group will be given 4 capsules twice daily with warm water, half an hour after breakfast and dinner. The Y-C and N-C groups will receive the placebo. The dose and usage of the placebo in the Y-C and N-C groups will be similar to that in the intervention groups. The treatment for the four groups will last 6 months.

In each center, every participant will be assigned a clinical research coordinator (CRC) responsible for allocating drugs based on whether they have clinical manifestations of brain damage and recruitment sequence before filling out the dispensing record form.

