### Randomization

This study uses a stratified block randomization approach. The participants were grouped into HT-CSVD with clinical manifestations of brain damage and HT-CSVD without clinical manifestation of brain damage based on the presence or absence of clinical manifestations of brain damage. An appropriate block length was selected (the size of block is 4) and random assignment was conducted using the SAS 9.4 statistical software (SAS Institute, North Carolina, United States) developed by statisticians from the Drug Clinical Evaluation Research Center of Central South University. 194 random sequences were generated for each group, that is, the randomized coding table with No. 001-194 was developed. The participants of each group were randomly divided into the intervention group and the control/placebo group at an allocation ratio of 1:1. Randomized codes were used as the drug numbers which were kept in an opaque sealed envelope and taken to Hinye Pharmaceutical Co., Ltd. (Changsha Hunan, China) for unified drug label production. The identification code of each subject was similar to the drug number.

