### Sample size calculation

At present, there is no clinical research report on TCM treatment for WML of CSVD. According to our previous case-control study, Fazekas grades of WML are an independent risk predictor of stroke (*p* < 0.01). With WML levels of 0–3 increasing step by step, delayed memory, spatial, and executive dysfunction appear at WML level 2, specifically at WML level 3. The mean ± standard deviation (SD) of Fazekas scores of HT-CSVD patients was 2.29 ± 1.26 (Zhou et al., 2022). After 6 months of NTF treatment, the mean ± SD of Fazekas scores is 2.29 ± 1.26 for the intervention group and 2.8 ± 1.3 for the control group (since CSVD is a progressive brain disease, we speculate that Fazekas grades of control groups will increase at least 0.5 points after 6 months without intervention). Considering α 10% significance level, the Z-value is based on the Z-value table for two-tailed distribution of 1.65. The β-value is determined at 0.20, and the Z-value is based on the Z-value table for a one-tailed distribution of 0.85. When the dropout rate is 20%, the sample size is calculated using an estimation formula for comparison of the mean values of two independent samples as follow:
$$N=\frac{{\left(Z_{\alpha /2}+Z_{\beta }\right)}^{2}*{\left(1+1/k\right)\;\sigma }^{2}}{\delta^{2}}=\frac{{\left(1.65+0.85\right)}^{2}*2*\left({1.26^{2}+1.3}^{2}\right)/2}{0.5^{2}}=81$$

Where N is the sample size of each group; Z_a_ is the table of Z-value for two-tailed distribution; Z_β_ is the table of Z-value for one-tailed distribution; σ is the standard deviation; δ represents the difference. The number of cases that may drop out is added; thus, 388 subjects will be required.

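### The Statistical analysis section leaves the Y/N randomisation stratum out of every named test and does not tie its list of tests to the two-arm comparison, while the sample size is built on four cells

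*Protocol article*

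**What the plan says.** **Design.** The section on group assignment states the stratification: "Participants will be stratified and denoted by Y or N according to the presence or absence of clinical manifestations of brain damage". The same section adds that "Different doses of NTF capsules will be given to the Y-T and N-T groups": the Y and N strata take the capsules at different daily frequencies, each with matching placebo. Under Randomization, "194 random sequences were generated for each group", where the groups are the two strata, and subjects in each are "randomly divided into the intervention group and the control/placebo group at an allocation ratio of 1:1".

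**Comparison.** The Abstract places Y-T and N-T in the intervention group and Y-C and N-C in the control group. Study design agrees: "Eligible participants will be randomly classified into the intervention group and control group". So does Primary outcome: "The Fazekas scores and dVRS grades will be obtained for both groups".

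**Size.** Sample size calculation gives 81 ("Where N is the sample size of each group") and a total of 388.

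**Analysis.** Statistical analysis names the t-test or ANOVA for normal data and Wilcoxon or Kruskal–Wallis otherwise, with "other potential confounding variables (such as multicenter characteristics) as covariates". A later sentence gives a non-parametric test or analysis of covariance for the therapeutic indexes. None of these sentences names the stratum or says which groups are compared.

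**The concern.** The word group means the two arms in Study design and Primary outcome, the two strata in Randomization, and (from the arithmetic behind 388) the four cells in the sample size. The analysis section offers tests for two groups and for several groups without saying which applies to the primary outcomes.

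The candidate analyses answer different questions. A pooled two-arm test asks whether Naotaifang works. Two within-stratum tests ask it separately for each population and regimen, with less power each and two chances of a positive result. A test across the four cells also responds to any difference between symptomatic and asymptomatic patients, and because regimen is fixed by stratum it cannot separate the two.

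A Y-N difference in lesion load is plausible on the article's own account. Cognitive decline is one of the manifestations that define Y, and Sample size calculation links cognitive dysfunction to higher white-matter lesion levels. The article gives no size for that difference.

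**Working it through.** **1. The plan's own figure.** Inputs from Sample size calculation: z = 1.65 and 0.85, SDs 1.26 and 1.3, difference 0.5, dropout 20%.
- σ² = (1.26² + 1.3²)/2 = 1.6388, so σ = 1.280.
- N = 2.5² × 2 × 1.6388 / 0.25 = 81.94 (stated as 81).
- 81 × 1.2 = 97.2, cut to 97, and 4 × 97 = 388.

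The total is reproduced only with four cells, so each within-stratum pair was sized on its own. It also matches 194 codes per stratum. (Dividing by 0.8 gives 4 × 101.25 = 405, so the plan multiplied by 1.2. That is a separate matter.)

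**2. Power by contrast** for a difference of 0.5, two-sided 10%: Φ(0.5 / (1.280 × √(2/n)) − 1.645).

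| Contrast | n per arm | Power at 10% | Power at 5% |
|---|---|---|---|
| One stratum, no dropout | 97 | 86% | 78% |
| One stratum, 20% dropout | 78 | 79% | 68% |
| Pooled, no dropout | 194 | 99% | 97% |
| Pooled, 20% dropout | 155 | 96% | 93% |

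Two unadjusted within-stratum tests at 0.10 have familywise error 1 − 0.9² = 19% (9.75% at 0.05).

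**3. Four-cell ANOVA with no drug effect.** Assume a Y-N gap g on the raw score. The test is a non-central F on 3 and 4n − 4 degrees of freedom, with λ = 4n(g/2)²/σ².

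| n per cell | g (assumed) | λ | Positive at p ≤ 0.10 | Positive at p ≤ 0.05 |
|---|---|---|---|---|
| 78 | 0.25 | 2.97 | 39% | 27% |
| 97 | 0.25 | 3.70 | 46% | 33% |
| 78 | 0.5 | 11.90 | 90% | 83% |
| 97 | 0.5 | 14.80 | 95% | 91% |

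In simulation (78 per cell, g = 0.5) Kruskal–Wallis gives 89% and 81%.

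**4. The same test with the baseline taken into account.** On change scores, with equal progression in Y and N, the gap cancels and the test stays near its nominal level. With baseline-adjusted ANCOVA and correlation ρ, the gap becomes g(1 − ρ) and the SD σ√(1 − ρ²), so λ is multiplied by (1 − ρ)/(1 + ρ). With 78 per cell at p ≤ 0.10 and assumed ρ of 0.7, 0.8 and 0.9, the rate is about 30%, 23% and 16% for g = 0.5, and 15%, 13% and 11% for g = 0.25.

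**5. Pooled two-arm test without the stratum.** Its variance is σ² + g²/4, although the arms are balanced on the stratum. Simulated error under no effect is 9.3% (nominal 10%) and 4.3% (nominal 5%) at g = 0.5, and 7.1% and 3.2% at g = 1.0. Power for a difference of 0.5 stays near 96% at g = 0.5 and falls to 94% at g = 1.0. A stratum-adjusted test stays close to its nominal level (9.4–10.0% and 4.5–5.0%).

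**6. What adjustment gains for a smaller effect.** Take a difference of 0.25, two-sided 10%, 155 per arm.
- Unadjusted, g = 0.5: SD = √(1.6388 + 0.0625) = 1.304, SE = 1.304 × √(2/155) = 0.148, power Φ(0.25/0.148 − 1.645) ≈ 52%.
- Adjusted for stratum and baseline, ρ = 0.5: SE = 1.280 × √0.75 × √(2/155) = 0.126, power about 63% (62% in simulation).
- Adjusted, ρ = 0.8: SE = 1.280 × 0.6 × √(2/155) = 0.087, power about 89%.

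Most of this gain comes from the baseline score, which is already collected.

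**The case against.** The two-arm contrast is not absent. The Abstract, Study design and Primary outcome all describe it. A reader might infer from the list of tests that the plan prescribes a four-group efficacy test and that a Y-N gap alone would make the trial positive. The text does not support that. ANOVA and Kruskal–Wallis appear in sentences about numerical variables in general, just after the one on baseline description, and the efficacy sentence names only a non-parametric test or ANCOVA.

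The high false-positive rates need an assumed gap, raw scores and no adjustment. The pooled unstratified test and the within-stratum tests are valid. The covariate list is open, so the stratum is not excluded. Model terms are often left to an analysis plan, which is not shown, and the trial is Phase II and described as exploratory.

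All of this stands and limits the point. It does not remove the mismatch inside the article: two-arm wording for the outcome, four-cell sizing, and an analysis section that offers both kinds of test without linking either to a contrast or to the stratum.

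**Conclusion.** The point holds as a problem of specification. The analysis section does not use the randomisation stratum in any named test and does not tie its tests to the two-arm grouping, while 388 comes from sizing four cells of 97. The choice of contrast moves power from about 79% within a stratum to about 96% pooled, after 20% dropout, for a difference of 0.5 at two-sided 10%.

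The risk of a misleading positive result is conditional on applying a multi-group test to the four cells for efficacy. It is then about 39–46% for an assumed 0.25-point gap and 90–95% for 0.5, unadjusted on raw scores at p ≤ 0.10. At 78 per cell, baseline adjustment reduces it to about 11–30% across the two gaps and correlations of 0.7–0.9. A reader might also infer that pooling without the stratum is invalid. It is not: it is slightly conservative and loses precision.

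**What to change.** In Statistical analysis, state that each primary outcome (Fazekas total and dVRS grade) is compared as Naotaifang (Y-T + N-T) versus placebo (Y-C + N-C), by ANCOVA with treatment, Y/N stratum, centre and baseline score, or by a van Elteren test stratified by Y/N if a rank method is preferred. Report within-stratum effects and the treatment-by-stratum interaction as secondary. Do not use a four-group ANOVA or Kruskal–Wallis test as evidence of efficacy. State that Y-T versus N-T is not a randomised dose comparison.

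In Sample size calculation, add that 97 per cell gives about 79% power within a stratum and about 96% for the pooled contrast after 20% dropout (difference 0.5, two-sided 10%).

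If the sponsor prefers the two within-stratum contrasts as primary, that is acceptable with multiplicity control, given the 19% familywise error of two unadjusted tests at 0.10.

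The cost is wording only, with no new patients or data. The Blinding section keeps the codes sealed until the statistical analysis, so the choice should be recorded and dated before they are opened. Having two primary outcomes is a separate question that this change does not settle.

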#### Assessment data

After 3 and 6 months of treatment, the subjects’ clinical BP, main symptoms and signs, disease history and medication use, TCM syndrome scores, MMSE and HAMD-17 scores will be assessed. Laboratory examination results will be collected respectively, such as blood routine, urine and stool routine, liver and kidney function, blood lipids, FPG, HbA1c, myocardial enzyme spectrum and coagulation routine, and ECG. The onset time, cause, and treatment of AEs will be recorded in the case report form (CRF), including an analysis of whether AEs are associated with the IP, completion and suspension time of the trial. Brain MRI will be assessed after 6 months of treatment (included Fazekas scores, dVRS grades, number of LI and CMB).

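### LOCF in the ITT analysis carries the baseline MRI forward for every patient without a month-6 scan, imputing zero change in a disease that the plan assumes progresses

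*Protocol article*

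**What the plan says.** The Statistical analysis section of the protocol article gives one missing-data rule for efficacy: "FAS uses the last-observed-carried-forward method (LOCF) to adjust the missing data and complete ITT analysis". It makes no exception for imaging. The only other efficacy set it names is the per-protocol set of patients who completed 6 months of treatment.

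The primary outcomes are Fazekas scores and dVRS grades. On their timing, the Primary outcome section says "Brain MRI examinations will be performed before enrollment and after 6 months of treatment". The Assessment data section agrees: "Brain MRI will be assessed after 6 months of treatment (included Fazekas scores, dVRS grades, number of LI and CMB". The month-3 visit covers blood pressure, scales, laboratory tests and ECG, but no MRI. The LI and CMB counts, which are secondary, follow the same two-scan schedule.

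On the expected course, the Sample size calculation section starts from a patient mean ("The mean ± standard deviation (SD) of Fazekas scores of HT-CSVD patients was 2.29 ± 1.26"). For month 6 it assumes that "the mean ± SD of Fazekas scores is 2.29 ± 1.26 for the intervention group and 2.8 ± 1.3 for the control group", because "we speculate that Fazekas grades of control groups will increase at least 0.5 points after 6 months without intervention". It allows for 20% dropout.

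**The concern.** LOCF needs an earlier post-baseline reading to carry forward. The MRI outcomes have none, so the value carried is the pre-enrollment scan. The imputed change is then exactly zero, and it enters the analysis as if it had been measured.

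This conflicts with the plan's own premise about controls. On average they are expected to worsen by 0.5 points, yet a control without the month-6 scan is recorded as stable, which is the result the plan expects only under NTF. At the planned dropout, up to about one primary value in five could be supplied this way.

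Two consequences follow. If NTF works as assumed, the ITT estimate is diluted. If NTF does nothing and the arms differ in how many patients lack the scan, the arm with more missing scans looks better. The size and the error rate of the main result would then depend partly on the pattern of missing scans.

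**Working it through.** **Inputs from the article.** Assumed mean change: NTF 0 (2.29 before and after) and control +0.5. The planned means differ by 2.8 − 2.29 = 0.51, but the formula uses 0.5. SDs are 1.26 and 1.3. The significance level is set by "Considering α 10% significance level, the Z-value is based on the Z-value table for two-tailed distribution of 1.65", power is 80% and dropout is 20%. Randomization is 1:1 within each of two strata, with 194 codes per stratum. That gives 97 per treatment group within a stratum and 194 per arm with strata pooled.

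**The plan's own figure.** Pooled SD = √((1.26² + 1.3²)/2) = 1.280. N = (1.65 + 0.85)² × 2 × 1.280² / 0.5² = 81.94, which the article gives as 81. The total is reproduced by 81 × 1.2 = 97.2, taken as 97, and 97 × 4 = 388.

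**Expected difference under LOCF.** With missing-scan proportions d_C (control) and d_T (NTF):

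difference = (control change) × (1 − d_C) − (NTF change) × (1 − d_T)

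*If the planning assumptions hold (control +0.5, NTF 0):*
- 10% missing per arm: 0.5 × 0.90 = 0.45
- 20% missing per arm: 0.5 × 0.80 = 0.40
- 30% missing among controls: 0.5 × 0.70 = 0.35

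*If there is no drug effect (both arms +0.5):*
- 20%/20%: 0, no bias
- 25% NTF / 15% placebo: 0.5 × 0.85 − 0.5 × 0.75 = 0.05 in favor of NTF
- 30% NTF / 10% placebo: 0.5 × 0.90 − 0.5 × 0.70 = 0.10 in favor of NTF

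The unequal splits are illustrative. The article gives only the overall 20%.

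**Power on month-6 scores.** SE = 1.280 × √(2/n), and power ≈ Φ(difference/SE − 1.645), holding the SD at 1.280.

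| Analysis | n per group | Difference | SE | Power |
|---|---|---|---|---|
| LOCF, one stratum | 97 | 0.40 | 0.184 | 0.70 |
| Observed only, one stratum | 78 | 0.50 | 0.205 | 0.79 |
| LOCF, strata pooled | 194 | 0.40 | 0.130 | 0.92 |
| Observed only, strata pooled | 155 | 0.50 | 0.145 | 0.96 |

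The observed-only rows use 97 × 0.8 = 77.6 and 194 × 0.8 = 155.2. In both settings LOCF has less power than leaving the missing patients out.

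**Type I error at nominal two-sided 0.10, month-6 scores.** With b the false difference, the rate is 1 − Φ(1.645 − b/SE) + Φ(−1.645 − b/SE).
- 97 per group: b = 0.05 gives 0.113; b = 0.10 gives 0.150.
- 194 per arm: b = 0.05 gives 0.125; b = 0.10 gives 0.199.
- Equal missingness: 0.10 in both.

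**Change scores.** The article gives no SD of change. Assume 1.0, with 97 per group and 20% missing per arm. The LOCF variances of change are 0.8 × 1.0² + 0.8 × 0.2 × 0.5² = 0.84 (control) and 0.8 × 1.0² = 0.80 (NTF). Then z = 0.40/√(1.64/97) = 3.08, against 0.50/√(2/77.6) = 3.11 for observed patients, so power is about 0.92 against 0.93. The power loss nearly disappears, but the estimate is still 20% too small. In simulations at 194 per arm, with an assumed SD of change of 0.5 to 1.0, type I error was about 0.14 to 0.27 for 25%/15% and 0.30 to 0.64 for 30%/10%. On change scores the inflation is therefore larger.

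**The case against.** Several points on the other side are sound and limit the finding.

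- **Not every dropout is imputed.** A reader might infer that all who stop treatment are scored as stable. Only patients without a month-6 MRI are; someone who stops capsules but is scanned keeps the measured value.
- **Zero change is not implausible for everyone.** It is the mean the plan assumes under NTF, and on an integer 0–6 scale many individual controls may show no change. The conflict concerns the control average.
- **A reversed result is not shown.** Under the planning assumptions the LOCF difference is 0.5 × (1 − d_C), which cannot change sign. What is shown is dilution of a true effect, or a false benefit when there is none.
- **Power of 0.70 against the stated 80% is not the general result.** It applies to month-6 scores within one stratum. The article does not say that strata are tested separately, it refers to both groups, and it allows analysis of covariance. Pooled power stays above 80%.
- **Unequal missingness is hypothetical.** Capsule burden cannot explain it, since placebo has the same dose and usage within each stratum. Side effects and intolerance, which the Quality control section lists among withdrawal reasons, could differ by arm, but the article gives no evidence that they will.
- **Other mitigation.** The per-protocol analysis is largely free of this imputation, and the article calls the trial exploratory. However, the per-protocol set selects treatment completers, so it does not protect the randomized comparison. The Discussion also says that the results will guide treatment.

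Table 1 words the follow-up MRI timing differently from the body text. The two should be reconciled, but either reading leaves one post-baseline scan. None of these points removes the defect in the stated rule.

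**Conclusion.** The concern stands in a conditional form. The mechanism needs no outside assumption: LOCF without exception plus a single post-baseline MRI means that a missing scan is recorded as zero change.

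The consequence depends on the circumstances. Under the planning assumptions with 20% missing per arm, the ITT difference is 20% too small (0.40 instead of 0.50). The power cost is about 9 percentage points within a stratum and 4 with strata pooled on month-6 scores, and smaller on change scores or with ANCOVA. With no drug effect and equal missingness there is no bias. With no drug effect and more missing scans under NTF, the false benefit is 0.05 to 0.10 points for the illustrated splits, and type I error on month-6 scores rises from 0.10 to about 0.11 to 0.15 at 97 per group.

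The documents do not support calling the rule always biased, or always conservative. It should still be replaced, because it fixes the primary ITT estimate by a value that contradicts the plan's expectation for controls.

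**What to change.** Do not carry the baseline MRI forward in the primary FAS analysis. Before unblinding, amend the Statistical analysis section as follows for Fazekas scores, dVRS grades and LI/CMB counts:

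1. Replace LOCF with multiple imputation under missing at random. Use baseline score, treatment arm, Y/N stratum, center and the month-3 measures already collected (such as blood pressure, TCM syndrome score and MMSE) as predictors, followed by ANCOVA, which the section already allows.
2. Add one reference-based sensitivity analysis in which NTF patients without the month-6 scan are imputed from the placebo distribution.

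This needs revised wording and modest programming, and no new patients or data. The intervals will be wider than under LOCF because the uncertainty about missing scans is then counted.

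No change to the blood pressure, MMSE or TCM analyses is asked for here. Those outcomes have a month-3 reading, and this point shows no harm to them.
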